## Abstract

**Background:**

Abnormal cell growth that can multiply and transfer to other bodily parts is referred to as cancer. Chemotherapy is a standard treatment for cancer patients. During or after treatment, patients may have varying degrees of cognitive impairment caused by the drug, which can negatively impact their quality of life. Cognitive impairment brought on by chemotherapy is one of the most frequent side effects that occur both during and after chemotherapy. Cognitive effects after and during chemotherapy have not been addressed in patients.

**Objective:**

To evaluate the effectiveness of cognitive rehabilitation on cognition and quality of life in chemotherapy-induced cognitive impairment.

**Methods:**

In this Randomized Control Trial (RCT), 60 subjects with chemotherapy-induced cognitive impairments secondary to any cancer will be randomised into 2 groups by the sequentially numbered opaque sealed envelope approach. The cognitive functions will be measured as the outcome measures, which include all the recall strategies, executive function tasks, information processing speed, and attention.
Both groups will receive intervention every day for 4 weeks. Wilcoxon signed the rank test for data analysis, and students paired the “t” test, which will be used to study within-group effects. Mann-Whitney U Test and students Unpaired “t” Test will be used to compare groups at pre-treatment and post-treatment.

**Results:**

As of November 2024, we will enrol 60 participants, and the data collection process will start from November 2024- November 2025. The expected results of the effect of cognitive rehabilitation on cognition and quality of life in chemotherapy-induced cognitive impairment in cancer patients will be significant, and the expected results will be published at the end week of November 2025.

**Conclusions:**

The study design is a framework to plan and test the feasibility of the intervention. The cognitive therapy will improve the cognition in chemotherapy-induced cognitive impairment patients.

**Trial Registration:**

Clinical Trials Registry India CTRI/2024/04/065805; https://ctri.nic.in/Clinicaltrials/pmaindet2.php?EncHid=MTAyNTE1&Enc=&userName=

**International Registered Report Identifier (IRRID):**

DERR1-10.2196/66011

## Introduction

### Background

Cancer is the leading cause of death and a major limitation to increasing life expectancy in every nation across the globe. According to the World Health Organization (2019) [1], in 112 out of 183 countries, cancer was a primary cause of mortality before the age of 70, and it ranked third or fourth in 23 additional countries. While death rates from conditions such as stroke and coronary heart disease are declining, cancers have risen in prominence as a leading cause of mortality [2]. Patients with noncentral nervous system tumors often experience cognitive symptoms, commonly referred to as “cancer-related cognitive impairment” (CRCI). This condition, primarily studied following chemotherapy, involves deficits in working and short-term memory, attention, executive function, and processing speed. After chemotherapy, up to 75% of patients with cancer report cognitive problems, and approximately 35% continue to experience cognitive dysfunction for 5-10 years after completing treatment [3].

As a result of population growth and aging, as well as shifts in the distribution and prevalence of major cancer risk factors, the global burden of cancer incidence and mortality is continuously increasing. An estimated 58.3% of cancer deaths in both sexes and half of all cancer diagnoses are expected to occur in Asia, which is home to 59.5% of the world’s population. According to GLOBOCAN 2020 estimates, India is projected to record 2 million new cancer cases by 2040, a 57.5% increase from 2020 [2]. Chemotherapeutic drugs have significantly improved cancer survival rates since their discovery and development over the past several decades. The 5-year survival rate across various cancers is around 60%, with skin melanoma, breast cancer (BC), and prostate cancer showing the highest rates. However, all treatments have side effects. Chemobrain, chemofog, or chemotherapy-induced cognitive impairment (CICI) is among the most common adverse effects of chemotherapy [4].

CICI is primarily investigated through neuroimaging studies of the brain, which reveal decreased gray matter density in the frontal, temporal, cerebellar, and right thalamic regions [5]. The prefrontal cortex and hippocampus are the primary centers of learning and memory; therefore, any damage to these areas results in cognitive dysfunction [6]. Consequently, altered behavior and memory are associated with impaired neuronal functioning in the hippocampus and frontal cortex [7]. Moreover, changes in cerebral white matter, mitochondrial dysfunction, and depletion of neural progenitor cells in the dentate gyrus contribute to cognitive impairments [8]. However, limited information is available regarding the precise mechanisms involved. Triple therapy with methotrexate, doxorubicin, and cyclophosphamide has been shown to increase peripheral and central levels of proinflammatory cytokines while reducing anti-inflammatory cytokine levels. This imbalance in the cytokine system disrupts neural plasticity and impairs cognitive function. Neuroimaging studies have shown reduced dendritic spine development in this model [9]. In summary, chemotherapy negatively affects cognition. Current reports on BC survivors highlight the occurrence of CICI. Variations in cytokine concentrations and the degree of cognitive impairment are associated with different chemotherapy regimens and dosages. However, the onset of cognitive disturbances remains unclear. The cellular targets, chemical composition of the drugs, dosing schedule, and numerous other confounding factors all play significant roles in determining the central nervous system’s inflammatory or neurotoxic side effects. Peripheral inflammation may also contribute to cognitive problems. Therefore, it is essential to closely monitor the effects of each specific drug in both preclinical and clinical studies [10].

Methotrexate is one of the chemotherapeutic agents known to cause vascular damage through its antiangiogenic activity [11]. Overall, the complex nature of anticancer therapy and its multiple mechanisms of action may trigger multifaceted symptoms of cognitive disorders and behavioral toxicities. In both clinical and experimental settings, doxorubicin is commonly administered to patients with BC who subsequently exhibit cognitive impairment, structural abnormalities, and brain mitochondrial dysfunction [12]. Platinum-based agents (such as cisplatin, oxaliplatin, and carboplatin) disrupt protein synthesis by cross-linking mitochondrial DNA, which is more susceptible to irreversible mutation than nuclear DNA [13]. Studies in mouse models have shown that deep brain penetration and inhibition of neural stem cell proliferation underlie cisplatin-induced cognitive impairment [14].

Crucial regions of the cerebral cortex and peripheral neurons undergo structural degradation due to taxanes (paclitaxel or docetaxel). Studies in neuropathic rodent models have demonstrated that mitochondria are particularly susceptible to damage induced by taxanes [8]. Administration of the same drug combination for 4 weeks led to increased expression of interleukin-1β and tumor necrosis factor-alpha in the rat corpus callosum, while interleukin-10 levels were reduced, resulting in impaired working memory function [15].

In summary, chemotherapy adversely affects cognitive function. Current reports on BC survivors highlight the occurrence of CICI. Variations in drug dosage and cytokine concentration levels across different chemotherapy regimens are associated with differing degrees of cognitive impairment [16]. Research into the mechanisms underlying the development of these cognitive disorders is still ongoing. The deleterious effects of inflammation or neurotoxicity on the central nervous system largely depend on cellular targets, drug composition, dosage schedules, and other confounding factors. Cognitive disturbances may also arise from peripheral inflammation. Therefore, it is essential to closely monitor the effects of each specific drug in both preclinical and clinical studies [17].

Conventional treatment approaches include aerobic exercise and cognitive behavioral therapy. These involve activities such as brisk walking, jogging, cycling, and engaging in cognitive skill exercises or workbooks. Studies have shown that, in addition to medical treatment, combining cognitive and aerobic exercises helps reduce symptoms of cognitive impairment without causing complications. Therefore, such interventions should be recommended for all patients with cancer experiencing CICI.

### Objectives

To determine the effect of cognitive rehabilitation on improving cognition in patients with CICI across all cancer types.To compare the effectiveness of cognitive rehabilitation with conventional therapy in patients with CICI.To determine the effect of cognitive rehabilitation on improving the quality of life in patients with CICI across all cancer types.

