### Control Group

Participants will perform aerobic exercises and cognitive behavioral training daily. The program will include brisk walking, cycling, jogging, and cognitive skill activities for 45 minutes per day, 5 days a week, over 4 weeks. These activities will not require direct supervision.

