**Physical fitness**					
	Aerobic exercises [18] (frequency, intensity, interval, and time principle)	Brisk walking, jogging, and static cycling	Frequency: 5-6 times per week; intensity: easy to moderate, approximately 60%-75% of maximum heart rate.		

^a^N/A: not applicable.

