## Discussion

### Anticipated Findings

This study will evaluate and compare the effects of cognitive rehabilitation and conventional therapy on cognition in patients with CICI. It is anticipated that this framework will significantly enhance the cognitive functions of patients receiving cognitive therapy as an intervention alongside conventional management protocols.

We hypothesize that cognitive training will result in measurable changes in brain magnetic resonance imaging, including improved perfusion, enhanced white matter connectivity (particularly involving the hippocampus), and increased brain volume (including the hippocampus). We have designed a randomized controlled trial (RCT) to investigate the effects of cognitive training and physical exercise on cognitive functioning in patients with cancer who have undergone chemotherapy and reported cognitive difficulties confirmed by standardized and validated neuropsychological assessments. Several underlying mechanisms may explain the effectiveness of the therapies included in this study. Cognitive rehabilitation and active exercises (such as weight training, aerobic training, dance, and yoga) may enhance physical capacity by counteracting reduced activity levels during or after cancer treatment [23]. Furthermore, increased physical activity can positively influence mental health. Psychosocial therapies promote activity management and stress coping, thereby reducing fatigue. Cognitive rehabilitation enhances neuroplasticity, enabling the brain to reorganize and adapt in response to injury, and helps develop compensatory strategies that allow individuals to manage cognitive deficits more effectively. It also contributes to building cognitive reserve, thereby reducing the risk of cognitive decline and promoting resilience. Several RCTs have demonstrated the efficacy of cognitive rehabilitation in improving cognitive function and quality of life, as well as in reducing symptoms of anxiety and depression in individuals with CICI [24]. Meta-analyses have further shown that cognitive rehabilitation is associated with significant improvements in cognitive function, particularly in attention and memory [25].

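### Objectives 1 and 3 name no comparator, and the exercise aim has no randomised contrast: tie the claims to the between-arm difference once the arm descriptions are reconciled

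*Protocol article*

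**What the plan says.** **Objectives.** The Protocol article lists three. The first is "To determine the effect of cognitive rehabilitation on improving cognition in patients with CICI across all cancer types". The second is "To compare the effectiveness of cognitive rehabilitation with conventional therapy in patients with CICI". The third is "To determine the effect of cognitive rehabilitation on improving the quality of life in patients with CICI across all cancer types". Only the second names a comparator.

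**Stated aim elsewhere.** The Discussion (Anticipated Findings) says the trial was designed to "investigate the effects of cognitive training and physical exercise on cognitive functioning in patients with cancer". The Abstract's Conclusions state: "The cognitive therapy will improve the cognition in chemotherapy-induced cognitive impairment patients".

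**Arms.** Under Control Group, "Participants will perform aerobic exercises and cognitive behavioral training daily", and the programme there also includes cognitive skill activities. Table 2 gives the intervention arm domain-specific cognitive exercises and, under Physical fitness, "Brisk walking, jogging, and static cycling". Table 2 lists no cognitive behavioral training. The Statistical Analysis section describes the arms differently: cognitive training added to traditional physical treatment, against traditional physical treatment. Anticipated Findings likewise speaks of cognitive therapy given together with conventional management.

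**Analyses.** Trial Design (the text below Figure 1) and Statistical Analysis plan between-group tests (unpaired t, or Mann-Whitney). The Abstract's Methods add paired t and Wilcoxon signed-rank tests for effects within each group.

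**The concern.** Because objective 2 already asks for the comparison with conventional therapy, objectives 1 and 3 read most naturally as asking for the effect of rehabilitation itself. The only listed analysis that seems to serve that reading is the paired test within the rehabilitation arm. It cannot separate treatment from what happens to patients over the same weeks of chemotherapy, or from taking the same tests again.

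Three conclusions are at risk. An improvement seen within the rehabilitation arm could be reported as caused by rehabilitation whatever the arm comparison shows. A difference from an active control could be reported as if it were an effect against nothing. And the trial could be said to have evaluated physical exercise, which it does not vary.

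**Working it through.** **1. The plan's own figure.** The sample size is set for a between-group difference: 2 × (1.96 + 0.84)² / 0.8² + 1.96² / 4 = 24.50 + 0.96 = 25.46, so 26 per group, raised to 30 for dropout. The 26 reproduces. The 0.8 is (μ₂ − μ₁)/σ, a difference between arms. The trial is therefore sized for the comparative question, and nothing below changes that number.

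**2. What each comparison estimates.** Let B be the change common to all patients (chemotherapy, time, retesting), R the effect of cognitive rehabilitation, C that of cognitive behavioral training with cognitive skill activities, and E that of aerobic exercise. Assume the effects add.

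| Source of the arm description | Intervention | Control | Difference |
|---|---|---|---|
| Control Group text with Table 2 | B + R + E | B + C + E | R − C |
| Statistical Analysis section | B + R + E | B + E | R |
| Add-on to the full control programme (one reading of Anticipated Findings) | B + R + C + E | B + C + E | R |

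- E cancels in every row, so exercise has no randomised contrast on any reading.
- R by itself is obtained under the two add-on readings. Under the Control Group text with Table 2, only R − C is obtained.
- The between-arm difference is a valid estimate in every row. What it means depends on which description is right, and the document does not settle that.

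**3. What the paired test estimates.** Change within the intervention arm is B + R + E, or B + R + C + E. It is never R alone.

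**4. How often B alone could look like a benefit.** The document gives no value for B or for the pre-post correlation r, so these are assumptions: a net shift of 0.3 to 0.5 SD, and r of 0.5 or 0.7. The standardised mean change is dz = shift / √(2(1 − r)). The rejection rate of a two-sided 5% paired t test comes from the noncentral t distribution with n − 1 degrees of freedom and noncentrality dz × √n. With r = 0.7 and a shift of 0.3, dz = 0.3 / √0.6 = 0.387; with n = 26 the noncentrality is 0.387 × √26 = 1.975.

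| r | n | Shift 0.3 SD | Shift 0.4 SD | Shift 0.5 SD |
|---|---|---|---|---|
| 0.5 | 26 | 31% | 50% | 69% |
| 0.5 | 30 | 36% | 56% | 75% |
| 0.7 | 26 | 48% | 72% | 89% |
| 0.7 | 30 | 54% | 78% | 93% |

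These are rates of a significant within-arm change when no component of treatment works. A net downward shift, as chemotherapy might cause, would instead hide a real benefit.

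**5. Number of retests.** Selection of Participants implies baseline, one assessment after each of 4 cycles and 4 weekly visits (1 + 4 + 4 = 9). Trial Design and Participant Timeline describe only a pre and a post assessment around 4 weeks. The extent of retesting is therefore not established. The argument does not need it: a single pre-post pair already carries B.

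**The case against.** The strongest reply is that in a two-arm superiority trial the effect of a treatment ordinarily means its effect relative to control, and that the between-group tests deliver this for both cognition and quality of life. That stands. A reader might infer from the objectives that no comparison in the trial addresses objectives 1 and 3; the document does not support this. An active control changes the quantity estimated but does not remove it, and under the add-on description in Statistical Analysis the difference is the added effect of rehabilitation. What the reply does not explain is why objective 2 is listed separately, or which comparator is meant when the arm descriptions disagree.

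Second, no text assigns the paired tests to objectives 1 and 3. They appear only in the Abstract, beside between-group tests. This also stands: misuse of them is a risk left open, not something the plan announces.

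Third, the exercise phrase is one sentence in the Discussion and could describe the combined package in Table 2. That lowers its weight, but as worded it names exercise as something whose effect is investigated.

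Fourth, the drift and correlation values are assumed. That is so; they show what could happen, not what will.

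**Conclusion.** The point holds as one about what the trial may claim. Objectives 1 and 3 should be tied to the between-arm difference, because change within one arm cannot show that rehabilitation improves cognition or quality of life. The exercise aim has a contrast of zero by design under every description of the arms. The meaning of the between-arm difference is left open, R − C or R, by conflicting descriptions that must be reconciled.

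The first and third of these conclusions need no assumed figure beyond additive effects for the labels R and R − C. The size of the within-arm problem, 31% to 89% at 26 patients and 36% to 93% at 30, rests wholly on the assumed shift of 0.3 to 0.5 SD and correlation of 0.5 to 0.7.

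Randomisation, sample size and the between-group tests are untouched. The correction is worth making because it is nearly free and decides what the final report can conclude.

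**What to change.** 1. Reconcile Control Group, Table 2, Statistical Analysis and Anticipated Findings, so that each states the same content for each arm. The investigators must say which description is correct; the comparator cannot be written into the objectives before that.
2. Reword objectives 1 and 3 as effects on cognition and on quality of life relative to that stated comparator, answered by the between-group test. Objective 1 will then overlap with objective 2, and the two can be merged.
3. Label the within-group tests as descriptive, and state that no efficacy claim will rest on one arm alone.
4. Delete the mention of physical exercise from the aim in Anticipated Findings, or state that the randomised comparison does not address it.
5. Make the Abstract's conclusion comparative, for example: the trial tests whether cognitive rehabilitation is superior to the stated comparator.

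The cost is a few sentences. The downside is a narrower and less favourable claim.

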## Methods

### Trial Design

This is an equal allocation, parallel-group, 2-arm superiority study, with the sample size distributed equally between the 2 groups. Patients will be evaluated according to predetermined inclusion and exclusion criteria and will be recruited from Siddharth Gupta Memorial Cancer Hospital in Sawangi, which is affiliated with Acharya Vinoba Bhave Rural Hospital. After obtaining informed consent, eligible participants will be selected through simple random sampling using computer-generated random numbers. All patients will be informed about the study procedures and asked to provide written consent before participation. The trial will include patients with a medical diagnosis of cancer who are currently undergoing chemotherapy. Sequence generation will be performed using computer-generated random numbers.

The allocation concealment mechanism will involve simple random sampling. Study participants will be randomly assigned using computer-generated random numbers. Randomization will be conducted by a researcher not involved in participant recruitment. To ensure allocation concealment, opaque sealed envelopes will be used, which will be opened only after participants are deemed eligible for treatment by the research team. Data collection will be carried out after participants are assigned to their respective intervention groups, with outcomes assessed and recorded during the preintervention phase. Postintervention data collection will be conducted after 4 weeks of intervention.

In data management, information obtained will be summarized using frequency and percentage for qualitative data, and mean and SD for quantitative data. Figure 1 presents the CONSORT (Consolidated Standards of Reporting Trials) flow diagram outlining the study design. See Multimedia Appendix 1 for the SPIRIT (Standard Protocol Items: Recommendations for Interventional Trials) checklist.

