**Chemotherapy type**				
	Cisplatin	✓	✓	✓
	Paclitaxel	✓	✓	✓
	5-Fluorouracil	✓	✓	✓
	Carboplatin	✓	✓	✓
	Dacarbazine	✓	✓	✓
	Temozolomide	✓	✓	✓
	Nab-paclitaxel	✓	✓	✓
	Oxaliplatin	✓	✓	✓

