### Eligibility Criteria

#### Inclusion Criteria

Recently diagnosed patients with stage I to III cancers who are scheduled to receive a defined number of chemotherapy cycles involving platinum-based compounds.Patients currently undergoing chemotherapy treatment.Patients receiving taxane- or platinum-based compounds, including cisplatin, carboplatin, or oxaliplatin.Patients with grade I or II cognitive impairment as per the National Cancer Institute’s standard toxicity criteria.Patients scheduled to receive a minimum of 4 cycles of chemotherapy with any of the aforementioned platinum-based agents.Male and female patients aged between 14 and 70 years.Patients receiving chemotherapy drugs approved by the National Cancer Board.

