### Sample Size

The sample size calculation used the Cohen *d* formula to compare 2 means. The effect size (*d*) was estimated using the following equation:

Effect size = *d* = (*μ*_2_ – *μ*_1_)/*σ* = 0.8

Given a large effect size (*d*=0.8), the required sample size per group was determined using the following formula:

*N*=([1 + *r*]/*r*)([*Z*_1–α/2_ + *Z*_1–β_]^2^/*d*^2^) + (*Z*^2^_1–α/2_)/2(1 + *r*)

where *Z*_1–α/2_ at the 5% level of significance = 1.96; *Z*_1–β_ at 80% power = 0.84; ratio allocation (group 2/group 1) = 1.

Substituting these values:

n=([1 + 1]/1)([1.96 + 0.84]^2^/0.8^2^ + (1.96)^2^/2(1 + 1)

n=2×([2.8]^2^/[0.64])+(3.84/4)

n=2 × (7.84/0.64) + 0.96

n=2 × 12.25 + 0.96

n=24.5 + 0.96= 25.46

Rounding up, 26 participants per group are required. Considering a 15% dropout rate (approximately 4 participants per group), the final sample size will be 30 participants per group, totaling 60 participants for the study.

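### The protocol treats chemotherapy regimen as related to the degree of impairment, but its stated arm comparison does not adjust for regimen, so precision is left unused and chance imbalance uncorrected

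*Protocol article*

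**What the plan says.** **Regimen and impairment.** The Introduction's Background says twice that the degree of impairment varies with regimen and dosage. In the second place it says that variations "across different chemotherapy regimens are associated with differing degrees of cognitive impairment". Table 1 has a block headed "Chemotherapy type" in a column of confounders. The block has eight single-drug rows (cisplatin, paclitaxel, 5-fluorouracil, carboplatin, dacarbazine, temozolomide, nab-paclitaxel, oxaliplatin) and no row for combinations.

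**Eligibility.** One inclusion criterion reads "Patients receiving taxane- or platinum-based compounds, including cisplatin, carboplatin, or oxaliplatin". Another asks for at least four cycles of a platinum agent.

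**Allocation.** Under Trial Design: "This is an equal allocation, parallel-group, 2-arm superiority study", and "Study participants will be randomly assigned using computer-generated random numbers". Opaque sealed envelopes are used. No stratification factor is named.

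**Analysis.** The text after Figure 1 compares the groups by an unpaired two-tailed t test. Statistical Analysis repeats this, with Mann-Whitney if normality fails. No covariate enters either comparison. Balance is addressed only by tests of homogeneity at baseline.

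**The concern.** A baseline variable that predicts the outcome can be used in the design (as a stratum), in the analysis (as a covariate), or in both. This protocol names such a variable, plans to record it, and then states an allocation and a test that use it in neither. With 30 patients per arm, regimen can differ noticeably between arms by chance, and an unadjusted comparison carries that difference into the treatment estimate. A homogeneity test may flag the imbalance but corrects nothing. Outcome variance that regimen could explain also stays in the error term, so the test is less sensitive than the planned data allow.

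**Working it through.** **1. The plan's own figure.** Inputs from Sample Size: "at the 5% level of significance = 1.96", "at 80% power = 0.84", d = 0.8 ("Given a large effect size"), ratio 1:1.

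n = 2 × (1.96 + 0.84)² / 0.8² + 1.96² / 4 = 24.50 + 0.96 = 25.46, rounded up to 26 per group. This reproduces. The 15% dropout allowance gives 26 × 1.15 = 29.9, hence the stated 30 per group (26 / 0.85 = 30.6 would give 31, a minor difference). Two-sided t-test power at d = 0.8 with 26 per arm is 80.7%.

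**2. Overlap of the Table 1 rows.** Every eligible patient receives a platinum or a taxane. A patient counted under 5-fluorouracil, dacarbazine or temozolomide must therefore also appear in a platinum or taxane row. If the four-cycle platinum criterion binds, a paclitaxel or nab-paclitaxel patient must also appear in a platinum row. The eight rows are not mutually exclusive, so a single class per patient has to be derived before the variable can enter a model as one factor.

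**3. Chance imbalance.** Assume K of the 60 patients belong to one class and the split is 30 v 30. The number in one arm is then hypergeometric(60, K, 30). The probability that the arms differ by at least 6 patients (6/30 = 20 percentage points) is:

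| Assumed prevalence | K | P(difference ≥ 20 points) |
|---|---|---|
| 20% | 12 | 10.4% |
| 30% | 18 | 15.8% |
| 33% | 20 | 17.0% |
| 50% | 30 | 19.6% |

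The documents give no prevalence, so the range is an assumption.

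**4. Size of the shift.** Shift = imbalance × regimen effect. For an assumed effect of 0.5 to 0.8 SD, a 20-point imbalance moves the arm difference by 0.20 × 0.5 = 0.10 SD to 0.20 × 0.8 = 0.16 SD. The standard error of the standardised difference at 26 per arm is about √(2/26) = 0.28.

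**5. Type I error of the unadjusted t test.** In simulation with a 50:50 class it is 5.1% for a regimen effect of 0.5 SD and 4.8% for 0.8 SD, so it holds overall. In the roughly 7% of trials where the arms differ by 8 or more patients, it is about 8% and 11% respectively.

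**6. Precision from adjustment.** For a two-level class with prevalence p and effect g in SD units, the variance explained is R² = g² × p × (1 − p), and the effective effect size is 0.8 / √(1 − R²).

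- Low end, g = 0.5 and p = 1/3: R² = 0.25 × 2/9 = 0.056. Effective d = 0.8 / √0.944 = 0.82. Power with 26 per arm is 83%.
- High end, g = 0.8 and p = 1/2: R² = 0.64 × 1/4 = 0.16. Effective d = 0.8 / √0.84 = 0.87. Power is 87%.

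A weaker effect gives less: g = 0.3 at p = 1/2 explains 0.09 × 1/4 = 2% of variance, and the gain is then very small.

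**The case against.** The strongest reply is that unstratified randomisation is a valid design. It is unbiased in expectation, chance imbalance is part of what the standard error covers, and a shift of 0.10 to 0.16 SD is well below that standard error. The plan already meets its 80% target. No document gives a regimen effect or prevalence. The Background implicates several drug classes as well as dosage and schedule, and never says that taxane against no taxane is the contrast that matters. Age, sex and cancer type stand under the same confounder heading. Covariates are also often left to the analysis plan.

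Most of this stands, and it limits the point to efficiency. It does not remove it, because the article states which tests compare the arms and states them unadjusted, while itself tying impairment to regimen.

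A reader might infer more, and the documents do not support it:

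- *That the comparison is biased or its error rate broken.* Step 5 of the working shows that the overall type I error holds.
- *That the recorded variable is unusable.* Overlapping drug rows still contain the information. A class such as taxane-containing can be derived from drug-level records.
- *That a chi-square test on eight rows is invalid because expected counts fall below 5.* The protocol never assigns that test to chemotherapy type, the threshold is a rule of thumb, and overlapping rows mean that 30 is not the ceiling on entries per arm.
- *That an imbalance would go unseen because Table 1 is laid out by enrolment, completion and dropout.* Nothing says Table 1 is the only baseline table.

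**Conclusion.** The point holds as a matter of efficiency and consistency. The protocol names regimen as related to impairment and as a confounder, then states a comparison that does not use it. The consequences are a 10% to 20% chance of an arm difference of 20 points or more in a two-level class (assumed prevalence 20% to 50%, equal arms of 30), with no correction planned, and forgone power of roughly 2 to 6 percentage points (81% against about 83% to 87%). The power figures rest on an assumed regimen effect of 0.5 to 0.8 SD, about 5% to 16% of outcome variance, and would be smaller if the entry rules leave little regimen contrast among those enrolled. The change is worthwhile because it is cheap, not because the trial would otherwise be invalid.

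**What to change.** 1. Reconcile the two inclusion criteria on drug class with each other and with the Table 1 drug list. The regimen class cannot be defined until this is settled.
2. Before outcome data are analysed, define one mutually exclusive regimen class per patient, derived from the recorded drugs; taxane-containing, yes or no, is one example. Derive it from each patient's full drug record, because the Background names docetaxel as a taxane and Table 1 has no row for it.
3. Make the arm comparison a linear model with this class as a prespecified factor.
4. Tabulate the class by arm.
5. Stratify the envelopes by class only if allocation has not yet taken place. The Results section reports 60 participants enrolled by November 9, 2024, while the abstract still puts enrolment in the future, so this step is probably too late.

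Cost: one derived variable, one model term and one degree of freedom. No extra patients, visits or procedures, and the sample size stays at 30 per arm.
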